#### Interim analyses {21b}

No interim analysis is planned.

#### Methods for additional analyses (e.g., subgroup analyses) {20b}

Since eligibility criteria may select patients without massive bleeding due to imperfect accuracy of the ABC score or wrong clinical judgment, primary and secondary outcomes will also be tested in the population with a massive transfusion (3 RBC within the first post-traumatic hour or at least 10 RBC at day 1).

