### Eligibility criteria {10}

#### Inclusion criteria

All consecutively admitted adult patients at risk of massive transfusion after severe trauma are screened for enrolment. Patients older than 18 years, admitted directly from the injury scene to a level-I trauma center, are eligible provided that they have two criteria: (1) a transfusion of at least one unit (U) of RBC prior to hospital admission or within the first hour after their admission (a delay of 90 min is tolerated if transfusion is decided within 1 h post admission) and (2) prediction by an assessment of blood consumption (ABC) score ≥ 2 [14] or by physician judgment of the need for a massive transfusion (defined by a transfusion of at least 10 RBC during the first 24 h or 3 RBC during the first hour).

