#### Outcomes {12}

The primary outcome is the total number of blood products transfused within the first 24 h after hospital admission, including RBC, FFP, and platelets. The choice of this primary outcome is based on the following rationale. First, a recent randomized control trial exploring the effect of vasopressin use after severe trauma on the same endpoint [20], Second, even if transfusion is considered a pillar in the management of acute bleeding, blood products are associated with adverse events and poor clinical outcome [11, 21]. Third, mortality after severe trauma is a complex process depending on hemorrhage but also on traumatic brain injury and pre-existing medical conditions, specifically in elderly patients [22]. We thus believe that 24h total blood consumption is an accurate proxy of the severity of the bleeding until the hemorrhage stops.

Secondary outcome measures are (1) number of separate units (and volume) of RBC, FFP, and platelets and transfused in the first 24 h; (2) time to achieve prothrombin time ratio < 1.5; (3) time to hemostasis, defined as the time necessary to control bleeding in the surgical field (operative field is dry without further foreseeable homeostatic procedures) or to control contrast blush after embolization during an interventional radiology (no more dye flushing); (4) number of thrombo-embolic events at 28 days; (5) mortality at 24 h and 28 days; (6) intensive care unit (ICU)-free days (number of in-hospital days outside ICU) within the first 28 days; (7) ventilator-free days during ICU stay within the first 28 days; (8) hospital-free days within the first 28 days; (9) hospitalization status at day 28; (10) GOSE for patients with brain lesions on initial scan; and (11) cost of each strategy at days 8 and 28. Cost analyses will be performed on expensive care: blood products and procoagulant treatments administered, imaging exams, surgeries, and length of stay in each healthcare unit.

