#### Participant timeline {13}

All consecutive trauma patients admitted directly from the injury scene who require RBC transfusion with a risk of massive transfusion are screened on admission. Eligible patients are then rapidly enrolled by the study investigator. They should be randomized and treated accordingly within 60 min post-admission. After patient treatment, follow-up includes hourly visits until 6 h post-admission, as well as visits at 12 and 24 h to measure prothrombin ratio, assess hemorrhage control and monitor adverse events. Thrombo-embolic events are under special scrutiny during the entire hospital stay because they are frequently expected adverse effects of PCC treatment. Each suspicious thrombo-embolic event should be confirmed with venous Doppler echography or angiography and treated following standard practice. Thromboprophylaxis is left to physician discretion. Patients are followed for 28 days with the last visit aiming at collecting the Glasgow outcome scale extended (GOSE) for patients with brain lesions on initial cerebral imaging, mortality, and place of living (Fig. 1).

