## Discussion

The PROCOAG trial explores the management of post-traumatic coagulopathy using pro-thrombin concentrate complex (PCC) in addition to standard blood products and fibrinogen. As opposed to fresh frozen plasma, PCC is readily available at admission and we hypothesized that early correction of coagulation factor deficiency optimizes patient blood management and therefore reduces the total number of blood products transfused within the first 24 h after hospital admission.

Hemorrhage is a leading cause of death in patients with trauma. Although blood products remain the standard for treating hemorrhagic shock, they are a limited and perishable resource. Moreover, concerns are increasing that blood products exert an immunomodulatory effect and negatively affect clinical outcomes [24–26]. Resuscitation strategies that decrease the need for transfusions without increasing complications, therefore, would represent a clinically important innovation.

Eligibility criteria were determined to select patients with severe acute bleeding early in the process so that PCC can be early administrated in the trauma bay on patient arrival. The study hypothesis states an empiric administration of PCC may enhance clotting capacity and decrease total blood product consumption. In consequence, the investigators expect several patients may not require a massive transfusion. The effect of the study protocol on massive transfusion will be investigated in a planned subgroup analysis (see above).

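### The massive-transfusion subgroup is defined partly by 24-hour RBC use, a component of the primary outcome counted after randomisation, so its comparison is not randomised and tends to understate a benefit

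*Protocol article*

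**What the plan says.** The Protocol article, under methods for additional analyses {20b}, states that "primary and secondary outcomes will also be tested in the population with a massive transfusion (3 RBC within the first post-traumatic hour"; the alternative route into the subset is a day-1 total of ten or more RBC units. Its reason is that the ABC score or the physician's judgment may have let in patients without massive bleeding.

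The 24-hour RBC count belongs to the primary outcome: "The primary outcome is the total number of blood products transfused within the first 24 h after hospital admission, including RBC, FFP, and platelets". Treatment starts well before that count is complete: "They should be randomized and treated accordingly within 60 min post-admission".

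The Discussion expects the treatment to change who is massively transfused: "In consequence, the investigators expect several patients may not require a massive transfusion". It then says: "The effect of the study protocol on massive transfusion will be investigated in a planned subgroup analysis (see above".

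At entry, massive transfusion is only predicted. The inclusion criteria define it as "at least 10 RBC during the first 24 h or 3 RBC during the first hour".

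**The concern.** A subgroup keeps the protection of randomisation only if membership cannot depend on treatment. Here one of two alternative routes, reaching 10 RBC by day 1, is something PCC is hypothesised to prevent. A patient whom PCC holds at 8 RBC leaves the PCC subgroup; the same patient on placebo might reach 11 and stay. What remains in the PCC subgroup is weighted towards heavier bleeders.

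The two parts of the article also treat the same patient differently. Section {20b} regards a patient without massive transfusion as a selection error to be set aside. The Discussion regards some of these patients as an expected consequence of treatment. If the Discussion is right, section {20b} removes responders, and mainly from one arm.

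The Discussion's stated aim, the effect on massive transfusion, cannot be met inside a set where everyone has had one. Because the subset is presented as the remedy for imperfect enrolment, readers will probably take it as the result in patients who truly bled.

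**Working it through.** **Inputs from the article.** 12 units in control and 9 under PCC (difference 3, or 25%); two-sided alpha 0.05; power 80%; 162 per group; the subgroup rule quoted above.

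**SD, which is not stated.** Solving n = 2(1.96 + 0.84)² SD² / 3² for n = 162 gives SD² = 162 × 9 / (2 × 7.85) = 92.9, so SD = 9.64. Allowing for Mann-Whitney efficiency of 0.955 or 0.864 gives 9.42 or 8.96. The 162 therefore fits an SD of about 9.0 to 9.6 but cannot be reproduced independently.

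**Simulation assumptions, none given in the article.** Total units are right-skewed (lognormal-Poisson) with mean 12 and SD about 9.6. RBC make up 50% of units. A share of units (0 to 25%) is given in the first hour and is unaffected by treatment. There are 1.5 million patients per scenario. Members have 3 RBC in that hour or 10 RBC in total.

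**Effect models.** Each gives an all-patient effect of about -3.0 units (-3.4 for the third).
- Uniform: every patient's use is multiplied by 0.75.
- Shift: 3 units fewer for each patient, as far as possible.
- Moderate bleeders: a reduction of up to 45% that fades out in heavy bleeders.
- Responders: 37.5% of patients have their use cut to 0.33 (0.375 × 0.67 = 0.25).

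The table gives the subgroup difference (PCC minus control, in units). The effect in patients who would be massively transfused under control is in brackets.

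| Qualify by first-hour route | Uniform | Shift | Moderate bleeders | Responders |
|---|---|---|---|---|
| 0-1% | -2.3 to -2.5 (-6.7 to -6.8) | +0.3 to +0.4 (-3.4) | +2.9 to +3.2 (-3.5) | -0.2 to -0.5 (-6.8) |
| about 4% | -3.2 (-6.6) | -0.4 (-3.3) | +1.6 (-3.5) | -1.8 (-6.6) |
| about 20% | -5.0 (-5.5) | -2.6 (-3.2) | -2.7 (-3.6) | -4.5 (-5.5) |

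With no treatment effect the difference was 0.0 in every run.

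**Membership.** Under the uniform effect with no early qualifiers, 17.9% of controls and 9.6% of PCC patients are members. With 162 per arm that is 162 × 0.179 = 29 against 162 × 0.096 = 16 patients.

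**Sensitivity.** A gamma-Poisson model using only the 10-RBC route gave 26.4 against 23.6 units under the uniform effect, a difference of -2.8 (ratio 0.90 where the all-patient ratio is 0.75). Membership fell from 20% to 11%. With an RBC share of 60% in the lognormal model, the uniform effect gave -2.2 to -2.3 units at 0-1% early qualifiers (true effect about -6.1).

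**The early criterion.** Section {20b} counts the hour from trauma; the inclusion criteria do not say from when. The table shows why this matters: the more patients enter by the early route, the smaller the bias.

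**The case against.** The strongest reply is that the two routes are joined by *or*. A reader might infer that 10 RBC is required for membership; it is not. A patient who qualified in the first hour stays in the subgroup however few units follow. That route is largely settled before or near the start of treatment (1 mL/kg at 120 mL/h takes 40 minutes for an 80 kg patient). This stands, and it limits the bias: with about 20% qualifying early, the loss under a uniform effect is only about half a unit.

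A reader might also infer that the subgroup will show harm from a drug that works. The documents do not support that. Reversal needed an effect concentrated in moderate bleeders, or in some models a constant shift, together with few early qualifiers. The article describes neither effect pattern and does not give the early share. A uniform version of its 25% reduction is attenuated and keeps its sign.

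Nor does the point undermine the trial's main result. This is an additional analysis, and the primary comparison is by intention to treat. In these simulations the subgroup was always less favourable to PCC than the truth, so it did not create a false claim of efficacy on blood use. Mortality, thromboembolic events and the other outcomes compared in the subgroup share the selection problem, but no size was computed for them.

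Finally, the authors' reason is fair: predictors at entry are imperfect. That explains the wish for such a subset but does not make its comparison randomised.

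**Conclusion.** The point holds in limited form and should be fixed. The 10-RBC route makes membership depend on response to treatment, so if PCC changes RBC use the subgroup arms are no longer comparable and the comparison tends to understate benefit. Under a uniform 25% reduction with almost no early qualifiers, about -2.3 to -2.9 units appear where the effect in patients massively transfused under control is about -6.7. Membership falls from about 18-20% to 10-11% of the arm. These figures rest on a back-solved SD of about 9.6 and an RBC share of 50%.

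The share qualifying early is unknown and decides how large the bias is. No scenario reversed sign when about 20% did so. Whatever the size, the subgroup cannot answer the Discussion's question about the effect on massive transfusion.

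**What to change.** 1. Report the proportion with massive transfusion by arm in all randomised patients, as a risk difference with a confidence interval. This is the analysis that answers the Discussion's question.
2. Replace the subgroup with one fixed by data available before randomisation, with a treatment-by-subgroup interaction test. Candidates are the ABC score, or RBC units given before randomisation if these are recorded separately. If the massive-transfusion subset is still shown, label it descriptive and non-randomised.
3. Reconcile the early criterion in section {20b} with the one in the inclusion criteria, so that both state the same starting point for the hour.

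The cost is mainly wording. The ABC score and early RBC transfusion already feature in the eligibility criteria, but the article does not say whether RBC units up to randomisation are captured as a separate item, so this must be checked. There is one small downside: a pre-randomisation subgroup only predicts massive bleeding and will not isolate the patients who truly bled.

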#### Methods in analysis to handle protocol non-adherence and any statistical methods to handle missing data {20c}

The analysis will be made following an intention-to-treat principle and a per-protocol principle to handle protocol non-adherence. We expect few missing data on the primary outcome since total blood consumption is always recorded and followed by the blood bank in each center.

#### Plans to give access to the full protocol, participant-level data, and statistical code {31c}

Information from the full protocol will be published in a peer-reviewed journal, and the study is registered in https://clinicaltrials.gov. The relevant data analyzed during the development of this study protocol are available upon request from the corresponding author.

### Investigational product handling and storage

Shipping of investigational products is under the responsibility of the coordinating clinical trial pharmacy of Grenoble University Hospital. Specifically, they create and ship randomization envelopes, and they order PCC (Kanokad®) to the manufacturer LFB (Les Ullis, France). The biopharmaceutical company LFB is responsible for producing and delivering Kanokad® to investing sites in respect of Good Manufacturing Practices. The coordinating pharmacy in Grenoble also orders and distributes saline solution and opaque devices required for the research to investigating sites. Each site is responsible for storage (2–8°C, away from light), handling and accounting of investigational products received. These elements are verified during monitoring visits.

#### Composition of the data monitoring committee, its role, and reporting structure {21a}

The sponsor appointed a data safety monitoring board (DSMB) that meets every year to analyze safety data (expected and unexpected adverse events). The DSMB is composed of members independent of the research and makes recommendations about protocol termination, modifications, or continuation without modifications.

#### Adverse event reporting and harms {22}

Adverse events are reported blinded to the sponsor by investigating sites and are analyzed by the sponsor safety departments following European regulation on clinical trials on medicinal products.

#### Frequency and plans for auditing trial conduct {23}

An audit initiated at the request of the sponsor or health authorities may be conducted at any time by trained, independent inspectors. The purpose is to ensure the quality of the research, the validity of its results, and compliance with the law and regulations. The auditors/inspectors must have direct access to the source and medical data and to any useful document related to the conduct of the clinical study. The confidentiality of the data and the anonymity of the subjects will be respected.

The investigators agree to comply with the sponsor’s and the competent authority’s requirements for an audit or inspection of the research.

The audit may apply to all stages of the research, from the development of the protocol to the publication of results and the classification of data used or generated in the research.

#### Plans for communicating important protocol amendments to relevant parties (e.g., trial participants, ethical committees) {25}

Any substantial modification, i.e., any modification likely to have a significant impact on the protection of participants, validity and on the results of the research, on the quality and safety of the products tested, on the interpretation of the scientific documents that support the conduct of the research, or on the methods of conducting the research, is subject to written amendment submitted to the sponsor; the latter must obtain, prior to its implementation, a favorable opinion from the ethics committee and an authorization from the national agency for drug safety. All amendments are validated by the sponsor and by all the research stakeholders concerned by the amendment before submission to the ethics committee and the national agency for drug safety. All amendments to the protocol must be made known to all investigators participating in the research. The investigators declare compliance with the protocol. Any amendment that modifies the management of the subjects or the benefits, risks, and constraints of the research is the subject of a new participant information note and a new consent form. The obtainment of informed consent follows the identical procedure as described above.

#### Dissemination plans {31a}

Results will be reported through scientific conferences and peer-reviewed publications following CONSORT recommendations [23]. All participants can be informed of the study results at the end of the trial on request.

## Discussion

The PROCOAG trial explores the management of post-traumatic coagulopathy using pro-thrombin concentrate complex (PCC) in addition to standard blood products and fibrinogen. As opposed to fresh frozen plasma, PCC is readily available at admission and we hypothesized that early correction of coagulation factor deficiency optimizes patient blood management and therefore reduces the total number of blood products transfused within the first 24 h after hospital admission.

Hemorrhage is a leading cause of death in patients with trauma. Although blood products remain the standard for treating hemorrhagic shock, they are a limited and perishable resource. Moreover, concerns are increasing that blood products exert an immunomodulatory effect and negatively affect clinical outcomes [24–26]. Resuscitation strategies that decrease the need for transfusions without increasing complications, therefore, would represent a clinically important innovation.

Eligibility criteria were determined to select patients with severe acute bleeding early in the process so that PCC can be early administrated in the trauma bay on patient arrival. The study hypothesis states an empiric administration of PCC may enhance clotting capacity and decrease total blood product consumption. In consequence, the investigators expect several patients may not require a massive transfusion. The effect of the study protocol on massive transfusion will be investigated in a planned subgroup analysis (see above).

The investigators acknowledge that total blood transfusion is only a surrogate marker of the severity of the bleeding. However, the AVERT Shock trial successfully applied this endpoint based on the rationale that reduction of blood transfusion is an objective of innovative trauma resuscitation [20]. The amount of transfusion has been shown to correlate with severe complications and poor clinical outcomes [10, 21, 27]. Specifically, Moore et al. noted that transfusion of packed red blood cells was the strongest predictor for the development of multi-organ failure (odds ratio = 8.6) [11]. The strategy tested in the present trial hence carries the potential to reduce morbidity, mirrored by the length of stay in ICU and the duration of mechanical ventilation, by reducing the amount of used blood products. The investigators are aware that despite existing guidelines, hemorrhage management may vary. This aspect is acknowledged by the center-based stratification of the randomization process.

Considering the fact that PCC use remains a matter of debate after severe trauma because of an associated potential high thromboembolic risk in this specific patient group; indeed, the use of PCC has repeatedly been shown to result in an excessive overshoot of thrombin generation in both in vitro studies [28, 29] and clinical studies including trauma patients [30]. PROCOAG Trial provides the advantage to explore the safety of empiric PCC administration based on the high clinical probability of active hemorrhage and massive transfusion.

As a pragmatic study, this trial aims at testing the effect of PCC administration in combination with standard care in a *real-life* context. With a high level of proof and quality standard, a positive result might already affect the management of severe trauma patients at risk of massive transfusion as this study investigates PCC efficacy, safety, and cost in this indication.

### Trial status

The trial has obtained all authorizations and recruitment started in December 2017. Enrollment is expected to be complete by June 2021. The protocol version reported here is version 6 as of February 6, 2019.

## Data Availability

Only the principal investigators, the DSMB, and the statisticians will have access to the final data set. There is no plan to share the data, but they are made available for audits and inspections. Anonymized patient data or a full set can be made available on reasonable request. Patients or their relatives are informed that anonymized data can be shared with other groups or used for further studies and have the opportunity to refuse personal data sharing.

## Abbreviations

DSMB: Data safety monitoring board
eCRF: Electronic case report form
FFP: Fresh frozen plasma
GOSE: Glasgow Outcome Scale Extended
ICU: Intensive care unit
NaCl: Normal saline
PCC: Prothrombin complex concentrate
RBC: Red blood cell
